| Patients who meet any of the following prerequisites will not be allowed to take part in this study:   - Women who are currently pregnant or breastfeeding - Cognitive impairment which prevents the patient from giving voluntary consent - History of any psychiatric conditions such as depression, psychosis, schizophrenia etc. - History of cancer in the past 5 years - History of abnormal renal or liver function - History of diabetes mellitus - Hepatitis B and/or Hepatitis C carrier - Diagnosed with tuberculosis (Positive microbiological evaluation for Grocott Methenamine Silver stain and Ziehl– Neelsen stain) - Any immunosuppressants or anti-inflammatory medications such as NSAIDS for the past 3 months - Concomitant medication that may have contraindication with prednisolone and methotrexate use |  |
| Withdrawal Criteria |  |
| Patients will be withdrawn from the study upon their request. However, data that has been collected until the time of withdrawal will be kept and analysed.  In cases of persistent non-compliance to dosing or study procedures, the data on non-compliance will be recorded, and the outcomes will be analysed based on intention-to-treat.  Under the following circumstances, patients will continue to be retained in the study to collect outcome data, but will be discontinued from taking the study drug:   - Serious allergic reaction to study drug requiring medical intervention and/or hospitalisation and as decided by investigators for safety reasons - Development of adverse drug reactions to the prescribed trial drugs which require medical intervention and as decided by investigators for safety reasons - Needing ventilator support upon hospitalisation, which prevents the consumption of tablets orally |  |
| Subject Replacement |  |
| There will be no replacement for patients who withdraw during the treatment period. |  |
|  |  |
| **4. TRIAL SCHEDULE** |  |

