| *Screening*  After patient is consented to the study, a baseline blood test (32mls, including pregnancy test, Hepatitis B test, Hepatitis C test, full blood count, liver function test and renal function test) and chest X-Ray will be conducted during the baseline visit to assess for eligibility prior to enrolment to the treatment phase. Additional research blood (14.5mls, 1 tablespoons) will be collected at this baseline visit for research purposes. Patient may be exempted from chest X-Ray and/or blood test if patient has done the same test within 30 days.  Baseline demographics and relevant clinical variables of patients will be collected. The following demographic and clinical variables will be collected: age of presentation, pre-menopausal or post-menopausal status, parity / breastfeeding status, concomitant rheumatic conditions, personal or family history of tuberculosis, smoking or alcohol intake, presenting complaint, unilateral or bilateral involvement, affected quadrant of the breast, duration of symptoms and previous antibiotics prescription for treatment of IGM.  Information on comorbidities will be evaluated to ensure suitability for both treatment arms prior to recruitment. Examples include drug allergies, plans for pregnancy, ongoing infection, previous history of cancer, previous tuberculosis, epilepsy, diabetes, hypertension, kidney, liver, cardiac problems, osteoporosis, glaucoma, peptic ulcers, previous side effects to either prednisolone or methotrexate.  If patient fulfilled all the eligibility criteria after screening assessment, she will be randomised to either of the treatment arm.  If patient did not meet the full eligibility criteria (eg. Pregnant, hepatitis carrier or abnormalities in renal or liver panels), she will not proceed to the treatment phase. The data collected and additional blood samples will be kept for analysis.  *Treatment Phase*  Patient will be scheduled to attend a clinical visit (T_0_) to either breast or rheumatology clinic if she meets all eligibility criteria for the initiation of treatment dose. There will be a window period of ± 7 days for this clinical visit. Patient is required to complete a pre-treatment quality of life online survey (approximately 10-15 minutes).  Patient will be scheduled for blood test (8mls, 0.5 tablespoons) and clinical visits to either breast or rheumatology clinic at the 1^st^ (T_1_), 2^nd^ (T_2_), 3^rd^ (T_3_) and 6^th^ (T_4_) month to assess their signs and symptoms, and drug compliance. There will be a window period of ± 14 days for each of these clinical visits. Additional research blood (14.5mls, 1 tablespoons) will be collected on the 1^st^ (T_1_) and 6^th^ (T_4_) months.  Patients are required to undergo a breast ultrasound to assess for their radiological response during the 3^rd^ (T_3_) clinical visit. A window period of ± 14 days will be applicable. The initial measurement of the breast lesion or mass will be recorded in three dimensions – i.e. anteroposterior, superior-inferior, mediolateral measurements. If complete clinical and radiological complete response has been achieved on the 3^rd^ (T_3_) visit, the doctor will discontinue the drug in a safe manner and no further breast ultrasounds will be required. If the patient’s symptoms or signs have not resolved by the 3^rd^ (T_3_) clinical visit, patient’s drug dosage will be assessed by the rheumatologist and treatment may be continued up to the 6^th^ (T_4_) month period and a repeat breast ultrasound will be required at the 6^th^ (T_4_) month. If symptoms have not resolved by the 6^th^ (T_4_) month of clinical visit, the patient’s drug dosage may be up-titrated or will be given an addition of a second therapy, i.e. combination therapy of steroid and methotrexate may be used. For clinical visits mention above, it will coincides with standard care visit.  During the clinical visits, Tingting Hu et al’s “M- score” will be adopted to grade the severity of the disease. M score is being calculated during clinical visits for IGM patients regardless of trial status for objective follow up. This is a common practice. For this study, the score will be administered by their attending healthcare professional (not limited to breast surgeons, investigators, or breast care nurses).  The M-score will be the sum of the following:  1) Mass score  2) Erythema score  3) Fistula score  4) Pain score  5) Quality-of-life (QoL) score  The scoring criteria were defined as follows:  1) Mass score: 0 for the absence of mass by palpation; 1 for mass ≤3 cm by palpation; 2 for mass >3 cm by palpation.  2) Erythema score: 0 and 2 for the absence and presence of erythema, respectively  3) Fistula: 0 and 2 for the absence and presence of fistula, respectively  4) Pain Score: 0 for Visual Analogue Score (VAS) 0-2; 1 for VAS 3-5; 2 for VAS 6-10  5) QoL score: 0 for absence of effects on QoL; 1 for mild effects on QoL, where the patient does not require medical assistant; 2 for serious effects on QoL, where the patient requires medical assistant  The total M-score ranges between 0 and 10 and serves as a quantitative and objective measurement of the severity of the symptoms.  The primary endpoint will be the clinical complete response (cCR) rate, which is defined as the proportion of patients who have an M-score of ≤ 1 at ≤1 years after treatment.  The secondary endpoints will be as follows:   - - The time to cCR, defined as the median time to cCR post randomisation.   - The treatment failure (TF) rate, defined as the proportion of patients with TF at 1 year post randomisation. The TF status will be defined as follows:     - If the patient has an M-score ≥6 before randomisation, TF is defined as the M-score remaining at ≥6 at 1 month post randomisation.     - If the patient has an M-score between 4 and 5 before randomisation, TF is defined as the M-score remaining at ≥4 and never being lower than 4.     - If the patient has an M-score <4 at baseline but never reaches cCR after randomisation, TF is defined as the M-score being >5 at the follow-up and remaining above 5 for one month. - Relapse rate, which is defined as the proportion of patients who have M-score >4 among the patients who achieved CR.   Throughout the course of the study, there are possible flares and relapse of the disease. Flares will be defined as any increase in M-score or lesion size on ultrasound whilst on therapy. While relapse will be defined as recurrence of symptoms or signs of IGM in the breast after previously experiencing complete resolution following therapy. If relapse occurs, patient will restart the same treatment arm for 6 months.  In the event of flares, blood test (8mls, 0.5 tablespoons) and additional research blood (14.5mls, 1 tablespoons) will be collected and the allocated treatment for the patient will be up-titrated by the doctor. In event of relapse, treatment for the patient will be reinitiated as per the allocated arm.  Additional research blood samples collected during the trial will be used for gene expressing profiling to identify unique patterns of gene expression that can be used to diagnose IGM and predict its treatment response.  Regardless of treatment arm, patient will be monitored by either breast surgeon or rheumatologist. Surgeons will assess for eligibility into trial, clinical reviews, and ultrasound breasts interpretation. Rheumatologists will be monitoring for drug side effects and titration if required. In event of failure of medical therapy, surgeons will have to intervene accordingly for aspiration or surgical drainage. In the event where patients require aspiration or surgical drainage during the study, methotrexate or prednisolone should be continued unless there is evidence of sepsis. The frequency of aspiration or surgical intervention will be recorded as events during the study.  Whenever the disease has been resolved during the study period, the balance medication and/or packaging will be retrieved to do medication accounting and checking for adherence to assigned treatment arm.  If side effects were to develop, doctors will evaluate the severity of the side effects and withdraw the patients from the trial if needed. |  |

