| *Follow up Phase*  The last clinical visit at the 12^th^ (T_5_) month may be a physical clinical visit or teleconsultation, depending on the doctor’s decision. Patient will be asked to complete a post-treatment quality of life online survey (approximately 10-15 minutes) during this visit. There will be a window period of ± 30 days for the last clinic visit. Please refer to Figure 1 for the study timeline. |  |
| **iii. Post Study Follow up and Procedures** |  |
| If there are any unresolved adverse events that require medical intervention, follow-up visits will be conducted and verified through the electronic medical records of their hospitalisation.  In the case of serious adverse events, this will be reported to the DSRB as soon as possible, no later than 7 calendar days after first knowledge by the investigator, and any additional relevant information about the event should be reported within 8 calendar days of making the initial report.  Patients’ clinical information and personal data may be combined or linked with, including but not limited to: government administrative data and research data such as, nation-wide health-related databases, economic data and National Autoimmune Registry, up to 31 December 2043. The linkage may be carried out by itself or with the assistance of a data intermediary. The collection of such data is for the purposes of the current research study and will be collected prospectively. |  |
| **iv. Discontinuation Visit and Procedures** |  |
| A discontinuation visit will be conducted for all patients who discontinued the study drug or withdrawn from the study regardless of whether it is voluntary based on patient’s request or decided by the Investigators for safety or non-compliance issues to follow-up on:   - Balance medication and packaging retrieval to do medication accounting and checking for adherence to assigned treatment arm - Existing AE(s) /SAE or complaints that are not resolved and to ensure that care assessment with support care delivery is continued until the problem is resolved. - Reason for withdrawal (if requested by the patient) |  |
| **TRIAL MATERIALS** |  |
| Trial Product (s) The investigational product (IP) and Auxiliary Product (AP) will be procured locally from NUH pharmacy and stored at NUHS Investigational Medicine (IMU) facility. |  |

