| **UPIRTSO events** refers to problems, in general, to include any incident, experience, or outcome (including adverse events) that meets ALL of the following criteria:   1. **Unexpected** 2. Pregnancy   In the event that the patient becomes pregnant during the study period, although very unlikely (patient will be screened for pregnancy before treatment phase and checked for pregnancy status at each clinical visit), patient will be withdrawn from the trial immediately. However, patient will be advised by their doctor or study investigator(s) on the procedures to stop medication.   1. Cancer   In the event that the patient is diagnosed with cancer during the study period, patient will be withdrawn from the trial immediately. However, patient will be advised by their doctor or study investigator(s) on the procedures to stop medication.   1. Fall risks   In the event that the patient falls during the treatment phase due to the side effect, doctor or study investigator(s) will assess and evaluate the severity of the fall before advising on the continuation of the study drug.  Expedited reporting to the IRB will be done as soon as possible, and not later than 7 calendar days after first knowledge by study investigator(s).   1. **Related or possibly related to participation in the research**   Prednisolone may cause mood changes (confusion, depression), weight gain, fluid retention, nausea, vomiting, indigestion, easy bruising, blood or black, tarry tools, blurred vision, increased urination or thirst, muscle weakness or cramps and severe stomach pain.  Methotrexate may cause mouth ulcers, nausea, vomiting, abdominal pain, diarrhoea, rash, hair loss, easy bruising, severe sore throat, tiredness, paleness, yellow eyes, tea-coloured urine, constant abdominal pain, risk of infection and breathlessness or persistent dry cough.   1. **Risk of harm**   Both prednisolone and methotrexate have been widely used clinically for treatments of other diseases and have a good safety profile.  The study investigators will make every effort to mitigate risks and ensure that the inclusion and exclusion criteria are strictly adhered to. Study investigators will also conduct close monitoring on the patients’ well-being during the clinical visits.  **Reporting Timeline for UPIRTSO Events to the NHG DSRB.**   1. Urgent Reporting: All SAE(s) listed whether related to or not to the study will be reported to IRB within 24 hours after first knowledge by study investigator(s):  - Results in death. - Is life-threatening (immediate risk of death). - Requires inpatient hospitalization or prolongation of existing hospitalization. - Results in persistent or significant disability/incapacity. - Is a medically important event.  1. Expedited Reporting: All collected study AE(s) will be reported as soon as possible, but not later than 7 calendar days after first knowledge by the study investigator(s). |  |

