| De-identified blood samples will be analysed and stored in NUH Tissue Repository. Recruitment and follow-up survey data will be collected electronically via NUHS REDCap. Only study team members with delegated rights will be able to access the data under the supervision of PI and Site-PI. All survey data will be collected electronically via FormSG. A copy of de-identified data will be stored in a secured server at NUH. |  |
|  |  |
| **SAMPLE SIZE AND STATISTICAL METHODS** |  |
| Determination of Sample Size |  |
| The prevalence rate of IGM in NUH is currently at 10 to 15 patients per year. Based on a stepped rule of thumb, a minimum sample size of 30 will provide at least 80% power to detect a medium standardised effect size of between 0.3 to 0.7 based on a randomised two-group comparison (Machin et al, 2021). Assuming a 20% attrition rate, the sample size required for this study is 36 patients. This will be rounded up to a sample size of 40 patients over a period of 36 months. |  |
| Statistical and Analytical Plans The primary outcome of 6-month clinical or radiological complete response will be compared between arms using Chi-square test. The effect estimate will be quantified in terms of difference in proportion as well as relative risk (RR) and their associated 95% confidence interval (CI). The secondary outcomes of time-to clinical or radiological response and time-to-relapse will be evaluated via the Kaplan-Meier method. The differences in survival curves will be compared using log rank test, with the effect estimate quantified in terms of hazard ratio and its 95% CI. The primary analysis of this trial will be based on Intention-to- Treat (ITT). A Per Protocol (PP) analysis will be performed on all patients who have completed 6 months of treatment regimen as a sensitivity analysis.  Chi square test will be used to evaluate the proportion of side effects and requirement for percutaneous or surgical intervention during treatment between arms. Modified Poisson regression will be used to identify clinical or biomarkers that are associated with treatment response and quantify the effect in terms of RR.  Patient reported outcomes will be reported via a survey on FormSG, conducted online. The questions will be adapted from SF36 V1 Singapore version and EORTC-BR23. Below are the domains to be compared:   - - General Health   - Physical Health   - Mental Health   - Body Image   - Sexual Image   - Breast Health |  |
| **ETHICAL CONSIDERATIONS** |  |

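### Section 6.3 lets doctors withdraw patients from the trial for side effects, while section 3.5 stops only the drug and keeps them for outcomes; the ITT comparison could lose treatment-related outcomes

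*Protocol*

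**What the plan says.** Three places in the protocol deal with a patient who has side effects.

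- **Section 3.5, Withdrawal Criteria.** In listed circumstances "patients will continue to be retained in the study to collect outcome data, but will be discontinued from taking the study drug". One of them is "Development of adverse drug reactions to the prescribed trial drugs which require medical intervention and as decided by investigators for safety reasons".
- **Section 6.3, last sentence of the Treatment Phase text.** If side effects develop, "doctors will evaluate the severity of the side effects and withdraw the patients from the trial if needed".
- **Section 6.3 iv, Discontinuation Visit and Procedures.** The visit applies to patients who stopped the drug and also to those "withdrawn from the study regardless of whether it is voluntary based on patient’s request or decided by the Investigators for safety or non-compliance issues". Its listed content is drug accounting, unresolved adverse events or complaints, and the reason for withdrawal. No M-score or ultrasound is listed.

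On data after withdrawal, section 3.5 says, directly after the sentence on withdrawal at the patient's request, that "data that has been collected until the time of withdrawal will be kept and analysed". Section 3.6 allows no replacement of patients who withdraw during treatment.

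Section 11.2 states the analysis: "The primary outcome of 6-month clinical or radiological complete response will be compared between arms using Chi-square test", with ITT as the primary analysis. Section 2.2 also lists relapse within one year among the primary objectives. Section 8.5 makes the trial open label, and section 2.1 hypothesises fewer side effects on methotrexate.

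**The concern.** ITT needs outcomes from randomised patients after they stop treatment as well as while they take it. Section 3.5 is written to secure that. Section 6.3 opens a way out of the trial for the same kind of patient, at the discretion of a doctor who knows the allocation.

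A patient withdrawn before month 6 stays in the ITT set but may have no 6-month outcome. One withdrawn between months 6 and 12 may have no relapse outcome. Such losses would be caused by treatment. Because the protocol itself expects the arms to differ in side effects, they could also be unequal between arms. With 20 patients per arm, each missing outcome counts for 5 percentage points of that arm's response rate.

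**Working it through.** **1. Is it the same event?** Section 3.5 covers reactions that need medical intervention and on which investigators decide for safety. Section 6.3 covers side effects that a doctor judges severe enough to act on. The 6.3 wording is wider, but the two overlap at the severe end, where withdrawal is most likely. There, 3.5 retains the patient and 6.3 permits removal. Section 6.3 iv does not settle the matter: it treats stopping the drug and leaving the study as separate categories and allows investigators to decide the second for safety, whereas 3.5 provides no such exit for adverse drug reactions.

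**2. Does the sample-size allowance cover it?** Inputs from section 11.1: minimum 30, attrition 20%, result 36, rounded up to 40.

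- The stated figure reproduces as 30 × 1.2 = 36.
- Dividing by the retained fraction gives 30 / (1 − 0.2) = 37.5, so 38.
- The final 40 covers both.

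The allowance protects the number of patients. It does not protect against loss that depends on treatment.

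**3. How much could be left undetermined?** The protocol gives no rate of withdrawal for side effects. Assumption: k = 1 to 4 of 20 per arm lack the 6-month outcome, the upper end being 20% of an arm. If every missing outcome could be a response or a non-response, the range of the risk difference has width (kA + kB) / 20:

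| Missing, one arm | Missing, other arm | Width |
|---|---|---|
| 1 | 1 | 2/20 = 10 points |
| 4 | 1 | 5/20 = 25 points |
| 4 | 4 | 8/20 = 40 points |

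The width depends only on the total missing, so it measures lost information and says nothing about imbalance between arms.

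**4. Which way could a bias run?** Assume that the true response is 12/20 = 60% in both arms and that k patients are withdrawn, all from one arm.

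- *Withdrawn patients are true non-responders and are left out:* the arm shows 12/(20 − k), that is 12/19 = 63%, 12/18 = 67%, 12/17 = 71% or 12/16 = 75% for k = 1 to 4. The false difference is 3 to 15 points in favour of the arm with the withdrawals.
- *Withdrawn patients would have been responders and are counted as non-responders:* the arm shows (12 − k)/20, that is 55% for k = 1 down to 40% for k = 4. The false difference is 5 to 20 points against that arm.

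The sign follows from the missing-data rule and from who is withdrawn.

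**The case against.** The best defence is that 3.5 is the dedicated section on withdrawal and states the retention rule explicitly, while 6.3 is conditional and may seldom be used. The sentence limiting data to what was collected before withdrawal follows the one on withdrawal at the patient's request, and nothing says that later data on investigator-withdrawn patients are discarded. Section 6.3 also says that the M-score is taken in routine care whether or not a patient is in the trial, so clinical response might be recoverable.

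This limits the point to outcomes that *could* be lost. It does not remove the conflict. The protocol makes no provision for using routine scores after withdrawal, and the M-score does not supply the ultrasound result.

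Four stronger readings are tempting, and the documents do not support them.

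- **That all the planned attrition can be charged to this rule.** The 20% in section 11.1 is a general allowance, not tied to side effects, and no split by arm is given.
- **That the loss can be scaled against a 13-point effect (94% less 80.7%, section 1.2).** Those rates come from separate reports, one on methylprednisolone, and describe a good response to treatment and disease improvement. Neither is 6-month complete response, and the protocol plans for no such difference.
- **That safety follow-up is cut short.** Section 6.3 iv follows existing adverse events to resolution, and 6.3 iii adds visits for unresolved events needing intervention. Only new events after withdrawal could be missed.
- **That section 9.2 contradicts 3.5 as well.** For pregnancy and cancer it says "patient will be withdrawn from the trial immediately", but neither event is on the 3.5 retention list.

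**Conclusion.** The inconsistency stands: for a side effect serious enough to act on, section 3.5 keeps the patient for outcomes and sections 6.3 and 6.3 iv allow removal from the study. If 6.3 is followed, the ITT comparison could lose 6-month and 12-month outcomes for treatment-related reasons, possibly unequally by arm.

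The size is unknown because the protocol gives no withdrawal rate. The range of 10 to 40 points rests on the assumption of 1 to 4 such losses per arm before month 6, with none recovered. A reader might infer that the less tolerable drug would be flattered. That holds if withdrawn patients are non-responders who are left out; other handling can reverse it, and such handling is commonly left to an analysis plan that is not at hand.

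This should be corrected, since no later analysis can restore outcomes that were not collected.

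**What to change.** Reconcile the last Treatment Phase sentence of section 6.3, and section 6.3 iv, with section 3.5. Both should say that an investigator's decision to stop study drug for side effects does not end outcome follow-up, and that scheduled visits and outcome collection continue to T5 unless the patient withdraws consent.

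Whether and when treatment is stopped is left as it is, and the pregnancy and cancer rules in section 9.2 are not rewritten.

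The cost is a few sentences of protocol text. The sample size stays at 40. The visits described under the Treatment Phase already coincide with standard care, and section 6.3 allows the T5 visit to be a teleconsultation.

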| This is a prospective pilot randomised trial to study the effectiveness of prednisolone versus methotrexate in achieving clinical or radiological complete response for women with IGM. The study will be conducted in NUH. This study evaluates the effectiveness of each drug in terms of clinical and/or radiological response, time to resolution as well as total number of flares over a period of one year follow-up. This study can potentially identify a more effective treatment with fewer side effects for women with IGM as well as personalize drug choices for patients who are at risk of frequent flares. |  |
| **HYPOTHESIS AND OBJECTIVES** |  |
| Hypothesis |  |
| The hypothesis is that methotrexate has a higher 6-month clinical or radiologically complete response with lesser side effects than prednisolone. The time to clinical or radiological response is shorter in the methotrexate arm compared to prednisolone arm. Relapse and time to first relapse is lower and longer in the methotrexate arm compared to prednisolone arm. |  |
| Primary Objectives |  |
| The primary objective is to evaluate the 1) Proportion of patients who achieved clinical or radiological complete response at 6 months 2) Time to clinical response and time to radiological response, and 3) Proportion of patients with relapse in one year within affected breast between each arm. |  |
| Secondary Objectives |  |
| The secondary objectives include evaluation of:   1. Side effects 2. Frequency of percutaneous or surgical intervention required 3. Potential biomarkers that may predict response to treatment: eg IL-6, CRP and neutrophil to lymphocyte ratio (NLR) 4. Patient reported outcome measures 5. Validate survey instrument for IGM patients |  |
| Potential Risks and benefits |  |
| End Points – Efficacy |  |
| Benefits expected for the patient are the total remission of IGM or reduced relapsed/flare of IGM. |  |
| End Points – Safety |  |

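### The month-12 visit may be a teleconsultation at the unblinded doctor's choice, but the M-score needs palpation, so M-score relapse and other late endpoints can lack a valid final assessment

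*Protocol*

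**What the plan says.** **Visit format.** Protocol section 6.3 (Follow up Phase) states that the last visit, at the 12th "month may be a physical clinical visit or teleconsultation, depending on the doctor’s decision". It adds: "There will be a window period of ± 30 days for the last clinic visit". No criterion governs the choice of format. Section 8.5 states that the trial is open label.

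**Schedule.** Figure 1 (section 4) shows visits at months 1, 2, 3, 6 and 12. Breast ultrasound is compulsory at month 3, discretionary at month 6 and absent at month 12.

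**Score.** The M-score in section 6.3 is the sum of mass, erythema, fistula, pain and quality of life (QoL), with range 0 to 10. The mass item is "0 for the absence of mass by palpation; 1 for mass ≤3 cm by palpation; 2 for mass >3 cm by palpation". The other two breast signs are "2) Erythema score: 0 and 2 for the absence and presence of erythema, respectively" and "3) Fistula: 0 and 2 for the absence and presence of fistula, respectively". No remote version of the score is given, and no rule for an item that was not examined.

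**Endpoints.** Section 2.2 lists as a primary objective: "Proportion of patients with relapse in one year within affected breast". Section 6.3 defines "Relapse rate, which is defined as the proportion of patients who have M-score >4 among the patients who achieved CR". It also defines clinical complete response (cCR) as an M-score of at most 1 within one year, and treatment failure at one year by three rules that depend on the baseline score.

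**The concern.** An endpoint defined by palpation is paired with a visit at which palpation may not take place. According to section 6.3, treatment stops at month 3 on complete response or may continue to month 6. Much of the time at risk for relapse off treatment therefore falls after month 6, and month 12 is the only scheduled look at it.

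The format is chosen by a doctor who knows the arm and has a view of how well the woman is. If calls go mainly to women who seem well, or more to one arm, relapse is ascertained differently between arms. With 20 women per arm (section 5.1), one misclassified woman moves an arm's proportion by 1/20 = 5 percentage points, and by more when the denominator is limited to responders. This is a gap in data collection: no later analysis rule can recover an examination that was not done.

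**Working it through.** **1. Reproduce the plan's range.** The items in section 6.3 are mass (0, 1, 2), erythema (0, 2), fistula (0, 2), pain (0, 1, 2) and QoL (0, 1, 2). This gives 3 × 2 × 2 × 3 × 3 = 108 patterns with sums from 0 to 10, as stated. Of these, 64 exceed 4, 44 exceed 5, and 104 exceed 1 (not cCR).

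**2. Video call, only mass unknown.** Let S be the sum of the other four items: 2 × 2 × 3 × 3 = 36 observable patterns, maximum 8. The patterns with S = 0, 1, 2, 3, 4, 5, 6, 7, 8 number 1, 2, 5, 6, 8, 6, 5, 2, 1 (total 36). Mass adds between 0 and 2, so a rule is undecided when S lies on one side of the cut-off and S + 2 on the other.

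**3. Telephone, only pain and QoL known.** Let R be their sum: 9 observable patterns, maximum 4, with R = 0, 1, 2, 3, 4 in 1, 2, 3, 2, 1 of them. The three unknown items add between 0 and 6.

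| Rule | Endpoint | Video: undecided when | Video: patterns of 36 | Telephone: undecided of 9 |
|---|---|---|---|---|
| >4 | relapse | S = 3 or 4 | 6 + 8 = 14 | 9 |
| ≥4 | failure, baseline 4-5 | S = 2 or 3 | 5 + 6 = 11 | 8 (R ≤ 3) |
| >5 | failure, baseline <4 | S = 4 or 5 | 8 + 6 = 14 | 9 |
| ≤1 | cCR | S = 0 or 1 | 1 + 2 = 3 | 3 (R ≤ 1) |

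**4. If unexamined items were scored 0** (an assumption; the protocol gives no such rule):

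- Video, score >4 missed: S = 4 with mass 1 or 2 (8 × 2 = 16) plus S = 3 with mass 2 (6), so 22 of 64.
- Video, score >5 missed: S = 5 with mass 1 or 2 (6 × 2 = 12) plus S = 4 with mass 2 (8), so 20 of 44.
- Video, false cCR: S = 0 with mass 2 (1) plus S = 1 with mass 1 or 2 (2 × 2 = 4), so 5 of 104.
- Telephone: the maximum is 4, so 64 of 64 scores >4 and 44 of 44 scores >5 are missed. R ≤ 1 covers 3 × 12 = 36 patterns, of which 4 are true cCR, so 32 of 104 non-responder patterns read as cCR.

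All of these count score patterns with equal weight. They are not patient frequencies.

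**5. Which endpoints use month 12.**

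- Not affected: the 6-month response in section 11.2, taken at a clinic visit, and the failure rule for baseline ≥6, which is read at month 1.
- Exposed: relapse after month 6, a first cCR between months 6 and 12, failure for baseline 4-5 (an incomplete sum below 4 would wrongly end the requirement never to fall below 4), and failure for baseline <4.

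**6. With an in-person visit** all five items are available and every cut-off above can be evaluated at that visit. The sample size does not change.

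**The case against.** The other side has several sound points.

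- **The main analysis is untouched.** Section 11.2 compares response at 6 months. cCR under section 6.3 can be reached at any earlier visit. Although section 2.2 makes one-year relapse a primary objective, sections 6.3 and 11.2 list relapse and time to relapse as secondary.
- **Relapse has a second route.** Section 6.3 also defines relapse as recurrent symptoms or signs after complete resolution. That needs no score, can be met partly by report, and leads to re-treatment when it occurs. Month 12 is therefore not the only way a late relapse can come to light. A recurrent mass that nobody palpates can still be missed, and the rule of M-score above 4 still lacks a complete score.
- **Only mass is tied to palpation.** That erythema and fistula need an in-person examination is inference. If both are seen on video, relapse is still decided in 22 of 36 patterns and cCR in 33 of 36.
- **An in-person visit does not settle everything.** The failure rule for baseline <4 also needs the score to stay above 5 for one month, which a single visit cannot show.

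A reader might go further and infer that one-year outcomes cannot be scored at all by teleconsultation, that failure can never be recorded, or that every error favours a good outcome. The documents do not support this. The first is true only of the complete score. The second overlooks the month-1 rule and the baseline 4-5 rule, where pain and QoL alone can reach 4. The third requires unexamined items to be scored 0. If the score is set missing, no direction follows.

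**Conclusion.** The point holds in a limited form and should be fixed, though it does not threaten the 6-month comparison. A complete M-score cannot be obtained remotely, and the protocol allows a remote visit at the only scheduled assessment after month 6. By telephone, relapse by M-score cannot be met. By video, it is undecidable in 14 of 36 observable patterns.

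The effect depends on how incomplete scores are handled, which the protocol does not state. Scored 0, relapse is under-detected. Set missing, the missingness may depend on arm and on apparent disease status.

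The number of women affected cannot be derived, because the protocol gives no expected share of remote visits. A reader might multiply an assumed share by 40 and call the result unclassifiable. That does not follow: some women will already have a settled cCR, relapse or failure status by month 12, and those who never responded fall outside the denominator of the relapse rate.

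**What to change.** In section 6.3, require the month-12 visit to be in person with a full M-score for every patient, within the existing ±30-day window.

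If only a teleconsultation takes place:

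- record the visit mode;
- treat the M-score as missing, and do not score unexamined items 0;
- derive no M-score-based cCR, relapse or failure status from the call;
- seek an in-person assessment within the window.

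The cost is a short text change and some calls converted to clinic visits, a format the protocol already permits. A few women may decline to attend, so the rule for a remote-only visit is needed as well. The change should be made before month-12 visits accrue.
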